### **5.1.6 Institutional Review Boards and Ethics Committees**

The Institutional Review Board or Ethics Committee has institutional responsibility for the safety of research subjects. The Institutional Review Board or Ethics Committee has the authority to terminate, suspend or require changes to a clinical trial.

### **5.1.7 National Regulatory Authority**

Since the national regulatory authority (such as the FDA for the U.S., or the MCC for South Africa) receives all expedited reports it also has the authority to terminate, suspend or require changes to a clinical trial.

## 5.2 Safety Surveillance During the Study

Subjects will be monitored and safety data collected by way of clinical interviews and examinations, evaluations conducted by study team members, and through reports of laboratory evaluations. Time points and the specific data collected for each of these evaluations are described in protocol appendices.

Through the 28-day period following each vaccination all **adverse events** observed by the investigator (or designee), or reported by the subject spontaneously in response to a direct question, will be medically evaluated and documented in terms of a medical diagnosis on the AE screen.

Through the entire study period all **serious adverse events** observed by the investigator (or designee) or reported by the subject spontaneously or in response to a question will be medically evaluated and documented on the AE screen.

## 5.3 Definition of Adverse Event

An adverse event (AE) is defined as any unanticipated problem involving risks to study participants or others. An adverse event, therefore, can be any unfavorable or unintended sign, symptom, disease, syndrome, abnormal laboratory finding, or concurrent illness that emerges or worsens relative to the subject's pretreatment baseline, whether or not it is considered to be related to the investigational product.

All conditions that exist prior to administration of the study vaccine (pre-existing conditions) will be recorded in the subject's medical history to establish baseline. Day-to-day fluctuations in pre-existing conditions that do not represent a clinically significant change in the subject's status will not necessarily be reported as adverse events.

Any adverse change from the subject's baseline condition (determined from evaluations conducted at screening/SD0 prior to initial vaccination and at SV4 prior to booster vaccination) that occurs following the administration of the study vaccine will be considered an adverse event. This includes the occurrence of a new adverse event or the worsening of a baseline condition, whether or not considered related to the study vaccine. Intermittent conditions such as headaches may be present on Study Day 0 but may represent an adverse event if the intensity or duration of the event is worse than usual following receipt of study vaccine. Adverse events include but are not limited to: adverse changes from baseline that represent increases in toxicity grade according to the Toxicity Table (see protocol appendices), adverse changes in the general condition of the subject, signs and symptoms noted by the subject, concomitant disease with onset or increased severity after study vaccine administration, and changes in laboratory safety parameters occurring after study vaccine administration.

**The reporting period for all adverse events is specified in Section 3.** Adverse events will be reported using a recognized medical term or diagnosis that accurately reflects the event. Adverse event evaluations will be reviewed by the principal investigator or by a designated medically qualified practitioner. Adverse event information are to be completed by members of the study

team designated in writing by the principal investigator. The onset and resolution dates of the event and action taken in response to the event will be documented. All adverse events must be followed until resolution is demonstrated, the condition becomes stable or until the end of the study. The resolution date will be recorded as the last date on which the subject experienced the adverse event or, if unresolved by the end of the study, the resolution date will be recorded as “ongoing.” Information recorded must be substantiated in the source documents. If an adverse event evolves into a condition that becomes “serious,” it will be designated as serious and a SAE Report (SAER) form will be completed.

## 5.4 Assessing Severity

The safety concepts of “severity” and “seriousness” are distinct concepts (see Section 5.8). Severity refers to a degree of clinical manifestation. “Seriousness” refers to defined outcomes from an adverse event. A severe adverse event is not always serious and a serious adverse event is not always severe.

For all adverse events, the investigator (or designee, who is a healthcare professional; is someone the investigator deems qualified to review adverse event information, to provide a medical evaluation of the event, and to classify the event based upon medical judgment and the severity categories described below) is responsible for assessing the severity of the event and the causal relationship of the event to the study vaccine.

The **severity** of all adverse events, including clinical findings and abnormal laboratory values, will be classified as one of the following grades:

1. **Mild**
2. **Moderate**
3. **Severe**

A Toxicity Table is provided in the protocol appendices for the assessment of severity of specified adverse events. The Toxicity Table Adverse Event Grades do not correlate directly with the classical severity grades of mild, moderate and severe. FOR THE PURPOSES OF RECORDING EVENTS ON THE AE screen, Toxicity Table Grade 1 events will be considered mild in severity, Toxicity Table Grade 2 events will be considered moderate in severity, and both Toxicity Table Grade 3 and 4 events will be considered as severe. In the Toxicity Table certain local reactions such as erythema (redness) and swelling are graded according to size. Laboratory values are graded according to level of deviation from the normal range.

For adverse events not listed in the Toxicity Table determination of severity requires some level of interpretation as outlined below. The degree of incapacity caused by the adverse event and the level of medical intervention required for treatment may be helpful in assessing the overall severity of the adverse event.

For example:

- “Mild” events are generally regarded as noticeable but have no impact on normal activities; they may or may not require over-the-counter treatment managed by the subject.

- “Moderate” events generally have some impact on an individual’s normal activities and may require general symptomatic medical intervention by a healthcare professional or by the subject.
- “Severe” adverse events may be incapacitating, leading to suspension of normal daily activities, and would generally require more immediate medical evaluation and intervention by a healthcare professional.

A change in severity of an adverse event will not be recorded as a new adverse event. Only the highest severity level that occurs during the entire period of the adverse event will be recorded with the onset and resolution dates encompassing the entire duration of the event.

## 5.5 Assessing Causal Relationship (Relatedness)

For all adverse events, the investigator and the sponsor (the local medical monitor) will determine a **causal relationship**, to the study vaccine without knowledge, for blinded studies, of whether MVA85A/AERAS-485, placebo, or active control was administered. A number of factors will be considered in making this assessment, including: 1) the temporal relationship of the event to the administration of the study vaccine 2) whether an alternative etiology has been identified and 3) biological plausibility. The investigator will use the following guidelines to assess the causal relationship of an adverse event to study vaccine:

- **Not Related** to study vaccine (i.e., there is no evidence of a causal relationship; another etiology is known to have caused the adverse event. The alternative etiology should be documented in the subject’s study record).
- **Unlikely Related** to study vaccine (i.e., there is less than a reasonable possibility that the adverse event was caused by study vaccine).
- **Possible** relationship to study vaccine (i.e., there is a reasonable possibility that the adverse event was caused by study vaccine. There must be a plausible mechanism for the event to be related to study vaccine. The evidence is inadequate to accept or reject, or favors rejection of, a causal relationship; an association exists between the event and the study vaccine but there may also be an alternative etiology, such as characteristics of the subject’s clinical status or underlying condition).
- **Probable** relationship to study vaccine (i.e., it is likely that the adverse event was caused by administration of the study vaccine. The evidence favors acceptance of a causal relationship; an association exists between the event and receipt of the study vaccine and there is a plausible mechanism for the event to be related to the study vaccine, and an alternative etiology is not apparent).
- **Definite** relationship to study vaccine (i.e., the study vaccine is known to be the cause of the adverse event. The evidence establishes a causal relationship; an association exists between the event and receipt of the study vaccine and there is a plausible mechanism for the event to be related to the study vaccine, and causes other than the study vaccine have been ruled out).

The principal investigator and the local medical monitor both determine causality. It is expected that communication and consultation may occur in the assessment of the causality of adverse events. The greatest degree of causal relationship (definite > probable > possible > unlikely

related > not related) determined by either the investigator or local medical monitor after their discussions will determine the ultimate classification of the adverse event. Definite, probable and possible are considered to be related. Not related and unlikely related are considered to be unrelated.

Every effort should be made by the investigator to determine the existence of any pre-existing conditions (e.g., mild nausea or headache on Study Day 0 with onset prior to study vaccination) that must be taken into consideration when assessing causal relationship of an adverse event. Pre-existing conditions should be recorded as baseline history and substantiated by appropriate source documentation. Intermittent conditions such as headaches or menstrual pain may not be present on Study Day 0 but may represent an adverse event if the intensity or duration of the event is worse than usual following study vaccine.

## 5.6 Definition of Adverse Reaction

An adverse reaction is an adverse event judged to be related to study vaccine (see Section 5.3 for adverse event definition).

**Related adverse events (adverse reactions) are defined as those judged by the investigator or local medical monitor to be possibly, probably, or definitely related to study vaccine.**

**The reporting period for all adverse events and adverse reactions is the 28-day post-vaccination follow-up period.** Adverse events and adverse reactions will be reported using a recognized medical term or diagnosis that accurately reflects the event.

## 5.7 Solicited Adverse Events and Injection Site Reactions

Solicited adverse events are events the subject is specifically asked about. These adverse events are commonly observed soon after receipt of vaccines. For this study, solicited adverse events include: injection reactions, diarrhea, vomiting and others. Solicited adverse events of local injection site reactions (i.e., pain at injection site, redness at injection site, or swelling at injection site) will be considered causally related to study vaccine (adverse reaction).

**The reporting period during which *solicited* adverse events will be asked of the subject is the immediate 28 day period following each vaccination.** The solicited adverse event reporting period begins with the day of vaccination.

Adverse events and solicited adverse events including assessment of local injection site reactions will be assessed by the investigator for severity, causal relationship to the study vaccine, possible etiologies, and whether the event meets criteria as a serious adverse event (and therefore requires immediate notification to the medical monitor).

Presence of ulceration and/or scarring at the site of injection and axillary lymphadenopathy of the injection arm(s) are considered to be adverse events that are causally related to the study vaccine and are of special interest. Site of injection ulceration (including presence of drainage)

and axillary lymphadenopathy will be actively evaluated during each clinic visit through the end of the study. These events will be recorded on the Adverse Event screen.

In the event that the clinical presentation meets the definition of a serious adverse event, an SAE Report must be completed and the event reported per protocol instructions.

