### 1.4 Clinical Experience with MVA85A/AERAS-485

A total of 20 clinical studies (15 Phase I, 5 Phase II) of MVA85A/AERAS-485 have been completed or are ongoing. A total of 309 healthy adults and adolescents, and 1674 children and infants, have received MVA85A/AERAS-485 in the completed studies, and over 300 subjects (including infants and HIV-infected adults) have been vaccinated in ongoing studies. The doses of MVA85A/AERAS-485 in these studies range from  $1 \times 10^7$  to  $1 \times 10^8$  pfu.

MVA85A/AERAS-485 induced high levels of antigen-specific IFN- $\gamma$  secreting T cells in BCG-naïve adults, and even higher levels in adults previously vaccinated with BCG either 1 month previously or 1-20 years previously. Immunogenicity of MVA85A/AERAS-485 in BCG-vaccinated adolescents and adults latently infected with *Mtb* was similar to that seen for BCG-vaccinated healthy adults.

Over 2000 individuals have received MVA85A in clinical trials to date, including BCG-naïve adults; BCG-vaccinated adults, adolescents, children, and infants; HIV positive adults; and adults latently infected with *Mtb*. Final safety data are available for 1870 of these subjects. No serious adverse events judged to be related to MVA85A have been reported in these subjects. The safety profile of MVA85A developed so far consists of local adverse events in most subjects, predominantly pain, erythema, swelling, and injection site warmth. Of these the vast majority were mild or moderate, although occasionally severe local reactions occurred. Less frequent systemic reactions resembled flu such as fever, headache, rash, malaise, fatigue, anorexia, cough, arthralgia, and myalgia. These systemic events were also usually mild or moderate. In a Phase II study in which over 1300 infants received MVA85A, systemic events related to study vaccination reported at a higher incidence (>1 percentage point difference) in the MVA85A

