group compared to control included irritability, insomnia, hypersomnia, pyrexia, hypophagia, somnolence, diarrhoea, and vomiting. The majority of these systemic events were mild or moderate, with severe cases reported in a few subjects (2 subjects for vomiting; 1 subject for pyrexia). Some adverse changes in haematology and chemistry parameters have been reported in adults and infants, which were mild to moderate in severity except for severe increases in infants for ALT (4 subjects), ALP (1 subject), and WBC (3 subjects); all severe changes returned to baseline levels on follow-up. In subjects infected with HIV, no clinically significant effect of MVA85A vaccination on CD4 counts or viral load was observed.

In a recently completed Phase 2b study,  $1 \times 10^8$  pfu MVA85A/AERAS-485 administered intradermally to BCG-vaccinated infants was shown to be safe and well-tolerated (10). The study did not, however, demonstrate any additional protection against TB disease or *M. tuberculosis* infection in MVA85A/AERAS-485-vaccinated infants compared to infants who received BCG alone. The immune responses to MVA85A/AERAS-485 as measured by *ex-vivo* ELISpot were modest (median 136 SFC per million PBMC) compared to responses seen in HIV-infected adults.

HIV-infected adults with CD4+ lymphocytes  $> 300-350/\text{mm}^3$  at study enrolment have received MVA85A/AERAS-485 and have been followed for at least 28 days post-vaccination, including some subjects who received a booster MVA85A/AERAS-485 vaccination 6-12 months after the first vaccination. The HIV-infected subjects in these studies included both adults receiving antiretroviral therapies (ART) and those not receiving ART. Local and systemic adverse events were similar to those previously observed in HIV-uninfected adults, including the frequency and severity of adverse events. Subjects on these studies were also followed for changes in CD4+ lymphocyte counts and HIV viral load. Injection with MVA85A/AERAS-485 did not appear to be associated with clinically significant declines in CD4+ lymphocytes or increase in HIV viral load. An antigen-specific immune response to MVA85A/AERAS-485 vaccinations was demonstrated in these studies, and booster vaccinations with MVA85A/AERAS-485 in an ongoing study showed an enhanced immune response (see TB019 below).

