| 7                 | DD/MM/YYYY |                                                                         | 0 1 2 3                                    | Yes / No | Yes / No | Yes / No                    |         |          |

Injection Site Pain Score

0 = No pain  
1 = Sensitive to touch  
2 = Partial restriction of activity  
3 = Pain restricts activity

[figure not shown]

Measure the size of redness and swelling by putting the ruler through both vaccine sites as shown (photo right). Record only the largest measurements at either vaccine site.

Record all signs you have experienced since the last time you recorded them, up to and including the time you take the measurements. Try to record everything at approximately the same time each day.

Subject Number

Please indicate if you have experienced any of these symptoms since you last recorded your symptoms.

Circle 'yes' or 'no' and, if yes, please also write the number of times

|                   |            | If these are only present at the injection site then please record as pain on page 2 |                    |          |                       |          |          |          |  |  |  |
|-------------------|------------|--------------------------------------------------------------------------------------|--------------------|----------|-----------------------|----------|----------|----------|--|--|--|
| Day after Vaccine | Date       | General muscle ache                                                                  | General joint pain | Unwell   | More tired than usual | Headache | Nausea   | Vomiting |  |  |  |
| 0                 | DD/MM/YYYY | Yes / No                                                                             | Yes / No           | Yes / No | Yes / No              | Yes / No | Yes / No | Yes / No |  |  |  |
| 1                 | DD/MM/YYYY | Yes / No                                                                             | Yes / No           | Yes / No | Yes / No              | Yes / No | Yes / No | Yes / No |  |  |  |
| 2                 | DD/MM/YYYY | Yes / No                                                                             | Yes / No           | Yes / No | Yes / No              | Yes / No | Yes / No | Yes / No |  |  |  |
| 3                 | DD/MM/YYYY | Yes / No                                                                             | Yes / No           | Yes / No | Yes / No              | Yes / No | Yes / No | Yes / No |  |  |  |

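### Section 5.7 names diarrhoea as a solicited event, but the Appendix E diary shows no item for it, so it may be captured less completely than the other solicited events

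*Protocol*

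**What the plan says.** Section 5.7 defines solicited events as those on which the subject is questioned directly, and then gives examples: "For this study, solicited adverse events include: injection reactions, diarrhea, vomiting and others". Diarrhoea and vomiting are the only two systemic events it names. The questioning period is fixed in the same section: "adverse events will be asked of the subject is the immediate 28 day period following each vaccination".

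Appendix C grades diarrhoea from Grade 1 to Grade 4, mainly by the number of stools in 24 hours.

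Section 5.8 gives subjects a diary to complete from the day of each vaccination through Day 7. It describes the diary as an aid to the conversation between staff and subject, and says its entries do not go straight into the eCRF.

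The second page of the diary (Appendix E) is introduced with "Please indicate if you have experienced any of these symptoms since you last recorded your symptoms". It asks for Yes or No, and for the number of times if Yes, on muscle ache, joint pain, feeling unwell, tiredness, headache, nausea and vomiting. A later table takes other symptoms as free text.

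Section 7.4.1 plans separate summaries of solicited events, including by severity and by relationship to vaccine.

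**The concern.** An event that Section 5.7 itself names as solicited appears to have no place among the diary's daily questions, although the diary is the only instrument in the protocol that prompts subjects between visits. Vomiting, named beside it in the same sentence, is prompted every day.

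The protocol gives some reason to want diarrhoea captured well. Section 1.4 reports vaccine-related systemic events that were more frequent on MVA85A than on control in the infant trial: "irritability, insomnia, hypersomnia, pyrexia, hypophagia, somnolence, diarrhoea, and vomiting". Diarrhoea is on that list.

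Safety is the primary objective. If one solicited event is collected with weaker prompting than the rest, its frequency in the solicited-event tables is not on the same footing as theirs. A low diarrhoea count could reflect how the question was asked and not what happened. The severity table is exposed too, because Appendix C grades diarrhoea by a 24-hour count, which is harder to reconstruct at a visit several days later than to note on the day.

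**Working it through.** **The plan's own safety figure.** Section 7.6 states that 325 vaccinees give a 90% probability of seeing at least one event of true rate 0.71%. The check is 1 − (1 − 0.0071)^325 = 0.9013, so the figure reproduces. It is a general statement about any adverse event and does not depend on the diary, so this point leaves it unchanged.

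**Side-by-side comparison of systemic events.**

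| Event | Section 5.7 | Appendix C, general systemic rows | Appendix E daily item |
|---|---|---|---|
| Vomiting | named | yes (row shared with nausea) | yes |
| Diarrhoea | named | yes | none visible |
| Nausea | not named | yes (row shared with vomiting) | yes |
| Headache | not named | yes | yes |
| Fatigue | not named | yes | yes (as tiredness) |
| Myalgia | not named | yes | yes (as muscle ache) |
| Joint pain, feeling unwell | not named | no row of their own | yes |

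Appendix C has five general systemic rows: nausea/vomiting, diarrhoea, headache, fatigue and myalgia. Four have a diary counterpart; diarrhoea is the fifth. Of the two systemic events named in Section 5.7, one has a diary item and one does not.

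**Extent of the difference in prompting.** The diary has one row per day for Days 0 to 7, that is 8 rows. With two vaccinations this gives 8 × 2 = 16 daily prompts per subject for each listed symptom, against 0 for diarrhoea. This assumes both vaccinations are given and the diary is used as issued. After Day 7 there is no diary for any event, so from then to the end of the 28-day window all solicited events are collected the same way, by interview.

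**What still collects diarrhoea.** Solicited events are reviewed and recorded at the Day 7 and Day 28 visits after each vaccination (Appendix A). Section 5.2 has all adverse events in the 28 days documented. The diary has the free-text table. A case reported by any of these routes enters the data and counts in the Section 7.4.1 comparison of subjects with at least one adverse event.

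**Size.** The protocol gives no expected diarrhoea rate in adults and no figure for how completely unprompted events are recalled, so the shortfall cannot be quantified from the documents. If blinding holds, any shortfall would be expected to be similar in the two arms. It would lower the observed rates and their difference without favouring one arm.

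**The case against.** The strongest reply is that the diary is not the data source. Section 5.7 makes the staff interview the means of solicitation for 28 days, Section 5.8 makes the diary an aid to it, and all adverse events in the window are documented anyway. This stands to a large extent. A reader might infer that the solicited tables will miss diarrhoea; the documents support only that they may. What remains is that the diary is meant to support that interview, and it does so for vomiting but not for diarrhoea.

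Second, the second diary table has three columns with blank headings in the extracted text, and one might be a lost diarrhoea column. Those columns carry no Yes/No cells, unlike every symptom column, so this is unlikely, but the original page should be checked.

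Third, the infant evidence is limited. The general systemic profile in Section 1.4 does not list diarrhoea, and other events on the infant list, such as irritability and insomnia, also have no diary item. The point therefore rests on Section 5.7 naming diarrhoea, not on a known adult signal.

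Three stronger readings are tempting and are not supported:

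- **Lost power for diarrhoea.** Section 7.4.1 plans Fisher's exact test only for subjects with at least one adverse event. Individual preferred terms get exact confidence intervals within arm. There is no planned diarrhoea test to lose power.
- **Relatedness will differ between sites.** Section 5.7 makes only some local reactions related automatically ("pain at injection site, redness at injection site, or swelling at injection site"), while the diary also lists warmth, itching and scaling, and Section 1.4 describes local events as "predominantly pain, erythema, swelling, and injection site warmth". But solicited events outside that rule "will be assessed by the investigator for severity, causal relationship to the study vaccine", under the written criteria of Section 5.5, with the local medical monitor also judging causality and the higher grade prevailing. Nothing shows that sites will diverge.
- **Warmth, itching and scaling should be related by rule.** That would be a preference, not the correction of an error. Section 5.4 also covers severity for events not in Appendix C, and tenderness in Appendix C overlaps the lowest positive pain score in the diary.

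**Conclusion.** The inconsistency is real but modest. Diarrhoea is named as solicited in Section 5.7 and graded in Appendix C, but has no visible item in the Appendix E diary, while vomiting, nausea, headache, fatigue and myalgia are prompted daily. Diarrhoea therefore rests on the visit interview and free text for Days 0 to 7 after each vaccination and may be captured less completely than the other solicited events in the Section 7.4.1 tables.

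This is a risk of uneven ascertainment, not a demonstrated loss of events or a bias between arms. Its size cannot be computed from the protocol, and no stated power or sample-size figure changes. The conclusion assumes that the extracted diary page is complete and that interview staff have no separate checklist that prompts for diarrhoea; the protocol shows none. The correction is worth making because it is cheap and serves data collection for the primary objective, and a gap in what subjects are asked cannot be repaired at analysis.

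**What to change.** 1. Check the original Appendix E page to confirm that there is no diarrhoea column.
2. If there is none, add a daily diarrhoea item to the second diary page, Yes/No with the number of times. That page already asks for a count, and a daily count matches how Appendix C grades the event.
3. Reconcile the Section 5.7 list of solicited events with the diary items, so that the Section 7.4.1 solicited-event tables use the events actually prompted.

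The cost is one diary column, a short edit to Section 5.7 and a diary version change. The change log (Sections 12.3 and 12.4) shows that the diary has been revised before, so the step is routine. The drawback is that subjects already enrolled used the existing diary. Diarrhoea should therefore be shown by diary version, so that a change in prompting is not read as a change in frequency.
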